### Control

Patients in Control will continue with the current care model. That means they will not receive the CPL. They will not participate in the CSP conversation but will continue to undergo their regular annual review consultation instead. However, during the consultation, they will receive a generic brochure that provides information about the available community programmes (common to both the Intervention and the Control) to support self-management. These patients will have to proactively sign up for these programmes.

### Training and support for the healthcare providers

All designated CSP practitioners attended a two-day PACE-D training workshop. The programme was facilitated by YoC-accredited trainers using training materials adapted from the YoC for the Singapore polyclinic context. The planned curriculum covered topics that ranged from the rationale and paradigms for CSPs, the processes involved, to hands-on skills-training for the conduct of CSP conversations. Content delivery occurred through a mix of presentations, role-plays, discussions and active reflection. This was followed by an additional CSP role-play practice session before they started CSP conversations with actual study participants. In all, there are 14 trained PACE-D CSP practitioners in NUP. Ongoing quarterly huddles are carried out by the trainers with these CSP practitioners to support fidelity to the intervention.

## Data collection

### Baseline data and questionnaire collection

The data collection points in PACE-D are summarised in Table 1. Upon enrolment, the PC administers a set of baseline questionnaires to capture details of socio-demographic profile (religion, current marital status, housing type, date of birth, ethnicity, gender, residential status, educational qualification), existing comorbidities (hypertension, hyperlipidaemia, ischemic heart disease, stroke, major depression, mood disorder of depressed type), anthropometric measurements (height and weight), healthcare utilisation in the past 1 year (for hospitalisation, emergency department visit, specialist outpatient clinic and the primary diagnosis of each visit), diabetes medication status (on anti-diabetes oral medication, on insulin therapy), lipid profile targets, [29] attendance at scheduled foot and eye screening in the past year, and self-care activities in the past year including smoking status, physical activity participation and community resource utilisation.

**Table 1 Tab1:** Data collection points at baseline, first annual review and second annual review for participants

Study overview					
	Recruitment	Annual Review (AR) 1			AR2
**Time point**	*−3 Month*	*− 3 Week*	*−1 Week*	*Year 0*	*Year 1*
	*Enrolment Visit*	*Annual Blood Panel*	*Care Planning Letter*	*Annual Review Visit*	*AR2 will be same as AR1 in sequence*^*a*^
**Enrolment**:					
Eligibility Screen & Informed Consent	✓				
**Study groups**:					
Control		✓		*Standard Care*	Y
Intervention		✓	✓	*CSP*	Y
**Variables collected**:					
**Primary outcome**					
*HbA1c*		✓			Y
**Secondary outcomes**					
*PAM-13*	✓			✓	Y
*Healthcare Utilisation Survey*	✓			✓	Y
*Healthcare Utilisation, Cost Data*	*Extracted from medical records, billing information, ePOS, Oracle BI*				
**Other pre-specified outcomes**					
*Body Weight and Blood Pressure*		✓		✓	Y
*LDL-cholesterol*		✓			Y
*Exercise, smoking status, community resource utilisation*	✓			✓	Y
*Foot and Eye Screening*	✓			✓	Y
*Survey on perception of the new care model (Intervention only)*				✓	Y

✓ *– Performed, collected, administered through survey (whichever applicable)*

Y *– Collected or performed in the same order as the various time points and sections detailed under Annual Review 1*

^*a*^*Patient will be returning for their annual blood panel test prior to the annual review. Patients in the Intervention will receive their care planning letter. Following that, the patients will go for the annual review where they receive either the standard care (Control) or CSP (Intervention)*

PAM-13 is administered on this first visit to determine baseline patient activation levels in all patients. The PAM-13 is a short form comprising 13 item measures that ascertain self-reported knowledge, skill and confidence in the self-management of the individual’s own health or LTC. Patient activation is scored in the range of 0–100 and categorised into 4 levels, with higher scores being reflective of greater levels of activation and greater capacity for self-management [23].

### Clinical data collection and follow-up assessments

Clinical outcomes data used for assessment is collected as part of routine practice for diabetes management in NUP, based on local clinical practice guidelines, and will be extracted from the EMR for purposes of this study. The clinical measurements are as listed in Table 1.

Survey questionnaires administered following each of the scheduled annual reviews include PAM-13, engagement in self-care activities, diabetes medication status (binary question on oral anti-diabetic medication and insulin therapy), and foot and eye screening attendance. Patients in the Intervention will receive an additional survey to rate their perception of the new care model. Results of routine blood tests, clinical markers and survey questionnaires administered throughout the study will be stored into REDCap, a secure browser-based platform for capturing of consent forms and research data electronically.

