### Study setting

PACE-D is conducted in the polyclinics at National University Polyclinics (NUP), the westernmost of three major administrative primary care healthcare groups in Singapore. Each polyclinic is staffed by 15–25 primary care physicians (PCPs) deployed in multi-disciplinary teams which include nurses and clinical pharmacists, with access to the psychologist, dietitian and medical social worker. In addition to the management of acute episodic conditions, the polyclinics provide for the efficient care of the patient with LTCs: laboratory services allow for rapid investigative reporting; surveillance programmes ensure the systematic detection of diabetic retinopathy, neuropathy and nephropathy; and workflows designed to target specific needs through the use of teamlets, [24] tele-consults, [25] and multidisciplinary case discussions [26, 27].

At the polyclinics under NUP, primary care is delivered to patients with LTCs through care teams known as teamlets. Each teamlet provides LTC care to a regular pool of approximately 5000 patients. It is formed by two PCPs and one care manager (CM) who is a chronic disease management-trained senior nurse. These three HCPs are supported by a care coordinator (CC) who schedules consultation and preventive health screening appointments for teamlet-empanelled patients.

In PACE-D, four of the six NUP polyclinics are involved in the study, with two of them designated as Intervention and the other two as Control. In each of these polyclinics, one teamlet is involved in the study and is supported by a PACE-D Coordinator (PC). The role of the PC is to recruit participants and obtain consent for participation, prepare the care planning letter (CPL) for mailing to the participants in the Intervention, and to administer questionnaires to all participants.

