#### Screening Adherence

Change in diabetes retinal photography rates, diabetes foot screening rates in patients

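### Foot and eye screening rates have only a coordinator-administered questionnaire as their named source, so arm differences in reporting can mix with differences in attendance

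*Protocol article*

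**What the plan says.** All references are to the protocol article.

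- **Outcome.** *Screening Adherence*, under the other pre-specified outcomes: "Change in diabetes retinal photography rates, diabetes foot screening rates in patients". *Statistical analyses* assigns past-year screening compliance to logistic regression.
- **Source at baseline.** *Baseline data and questionnaire collection* includes, in the questionnaire set given at enrolment, "attendance at scheduled foot and eye screening in the past year".
- **Source at follow-up.** *Clinical data collection and follow-up assessments*: "Survey questionnaires administered following each of the scheduled annual reviews include PAM-13, engagement in self-care activities", then medication status and, closing the list before the text moves on, "foot and eye screening attendance. Patients in the Intervention will receive an additional survey to rate their perception of the new care model". Table 1 ticks screening at enrolment and at the annual review visit, the same pattern as exercise, smoking and community resource use.
- **Who asks.** *Study setting* gives each clinic one study coordinator, whose duties include "to administer questionnaires to all participants" and, in the Intervention clinics, preparing the care planning letter.
- **Who delivers the screens.** *Study setting* says of the polyclinics that "surveillance programmes ensure the systematic detection of diabetic retinopathy, neuropathy and nephropathy", and that each teamlet is "supported by a care coordinator (CC) who schedules consultation and preventive health screening appointments for teamlet-empanelled patients".
- **Records already in use.** Clinical outcomes come from the EMR. Utilisation and cost come from the polyclinic and business intelligence systems. No record source is named for screening attendance.

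**The concern.** A retinal photograph or a foot screen is a dated service that the clinic performs. The plan names a questionnaire answer as its measure. That would be a modest loss of precision if the reporting error were the same in both arms, but three features of the design let it differ:

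- The follow-up question comes after the annual review. By then an Intervention patient has had a letter with results and condition-specific information and a planning conversation about diabetes. A Control patient has had a routine review and a generic brochure.
- Whole clinics are assigned to an arm and each has its own coordinator, so interviewer and arm cannot be separated. In the Intervention clinics that coordinator also prepares the letter and may help coordinate the patient's action plans.
- The enrolment answer is given before the intervention starts. Adjusting for it cannot remove a change in reporting that the intervention itself produces.

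What is at stake is the reading of one process outcome: a difference in reported rates could reflect attendance, reporting, or both.

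**Working it through.** **No figure to reproduce.** The article gives no screening rate, target difference or power for this outcome. The check is a trace of the data source, followed by an illustration under assumed inputs.

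**Trace.**

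| Item | Survey named? | Record source named? |
|---|---|---|
| HbA1c, LDL-cholesterol | No | Yes, EMR |
| Healthcare utilisation | Yes | Yes, records and billing |
| Exercise, smoking, community resources | Yes | No |
| Foot and eye screening | Yes | No |

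Screening is handled like the lifestyle items, which have no clinic record to draw on, although it is a clinic service. Utilisation, the nearest comparison, is taken from both sources.

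**Formula.** Let t be the true attendance rate, the same in both arms. Let Se be the share of attenders who report attendance, and FP the share of non-attenders who report it.

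- Reported rate = t × Se + (1 − t) × FP
- False difference = t × (Se_I − Se_C) + (1 − t) × (FP_I − FP_C)

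The sign therefore depends on both brackets, and the documents supply neither.

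**Sample size used.** From *Sample size calculation*: 1620 / 2 = 810 per arm; 810 × 0.70 = 567 completers per arm. The test is an unadjusted two-proportion z test at two-sided 0.05. It ignores clinic clustering, covariates and the imputation of missing endpoints.

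**Worked case (all rates assumed).** t = 0.75, FP = 0.20 in both arms, Se = 0.95 against 0.88.

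- Intervention: 0.75 × 0.95 + 0.25 × 0.20 = 0.7625
- Control: 0.75 × 0.88 + 0.25 × 0.20 = 0.710
- Difference: 0.0525
- Standard error: √[(0.7625 × 0.2375 + 0.710 × 0.290) / 567] = 0.0261
- z = 2.01; chance of a significant result = Φ(2.01 − 1.96) ≈ 0.52

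**Opposite case (also assumed).** t = 0.75, Se = 0.95 in both arms, FP = 0.10 in Intervention against 0.20 in Control, as if the conversation made patients readier to admit a missed screen.

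- Intervention: 0.7125 + 0.025 = 0.7375
- Control: 0.7125 + 0.050 = 0.7625
- Difference: −0.025
- Standard error: √[(0.7375 × 0.2625 + 0.7625 × 0.2375) / 567] = 0.0257
- z = −0.97; chance of a significant result favouring Control = Φ(0.97 − 1.96) ≈ 0.16

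**Range.**

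| t | Se, I / C | FP, I / C | False difference (points) | Chance of a significant result in that direction |
|---|---|---|---|---|
| 0.75 | 0.95 / 0.88 | 0.20 / 0.20 | +5.25 | 52% |
| 0.60 | 0.95 / 0.88 | 0.20 / 0.20 | +4.2 | 31% |
| 0.60 | 0.95 / 0.90 | 0.30 / 0.30 | +3.0 | 19% |
| 0.90 | 0.95 / 0.90 | 0.30 / 0.30 | +4.5 | 60% |
| 0.60 | 0.95 / 0.85 | 0.30 / 0.30 | +6.0 | 57% |
| 0.90 | 0.95 / 0.85 | 0.30 / 0.30 | +9.0 | 99% |
| 0.75 | 0.95 / 0.95 | 0.10 / 0.20 | −2.5 | 16% |
| any | equal | equal | 0 | 2.5% (nominal) |

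Modest differences in reporting accuracy are enough to matter at this sample size. The table does not show that such differences will occur.

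**The case against.** The strongest reply is that self-report is inferred. The enrolment questionnaire set also covers height and weight, the primary diagnosis of past visits and lipid targets, which suggests a form that is not pure recall. The coordinator works from the appointment register. The article says that clinical outcomes come from the EMR and that the clinical measurements are those in Table 1, where screening has a row, and the table key allows for more than one means of collection. This stands in part: a record source is not strictly excluded. But the follow-up text places screening attendance explicitly in the survey list, beside PAM-13 and self-care, and a general sentence about the EMR does not override that.

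A questionnaire also captures screens done by any provider, which clinic records do not. That stands and shapes the fix.

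Two stronger readings are tempting and should be resisted:

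- A reader might infer that the error will favour the Intervention. The documents do not support this. The letter's content is not shown, and the opposite case above is as compatible with the text.
- A reader might infer that the past-year recall window is detached from the annual reviews. The follow-up surveys are given at those reviews; only the enrolment questionnaire falls about 3 months before the first one.

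**Conclusion.** The point holds as a weakness in the choice of data source. For two services that the polyclinics perform and schedule, the only source named is a coordinator-administered questionnaire, answered after an arm-specific letter and conversation. The comparison can therefore mix reporting with attendance, and baseline adjustment does not cure that.

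The documents fix neither the direction nor the size of any bias. The 5-point gap and its 52% chance of significance rest wholly on assumed rates; with equal reporting accuracy in both arms the false difference is zero. The point reaches only an outcome in the other pre-specified tier. HbA1c, PAM-13, utilisation, cost and the sample size are untouched. If the full protocol or the data collection form already scores screening from records, one clarifying sentence would settle the matter.

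**What to change.** Score retinal photography and foot screening separately, each as done or not done, from polyclinic service dates. Use the same fixed 12-month window in both arms: the 12 months before the first annual review for baseline, and the 12 months before the second for the endpoint. A yes/no event should not be rescaled for length of follow-up; the fixed window makes that unnecessary.

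Keep the survey item to identify screens done outside National University Polyclinics, and add a sensitivity analysis that counts those as done. State the source of each in Table 1 and in *Clinical data collection and follow-up assessments*.

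The cost is a small addition to an extraction that is already planned, assuming that service dates for both screens can be retrieved, which the article does not confirm. The remaining weakness is that outside screens stay self-reported, so the record-based measure understates attendance for patients screened elsewhere. The sensitivity analysis shows how much that matters.

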### Healthcare cost and utilisation

Data related to healthcare cost and utilisation, specifically on the following, will be extracted by the National University Health System (NUHS) Academics Informatics Office.
Healthcare utilisation in hospitals, including visits to emergency departments and hospitalisations, and their corresponding primary diagnosis;Number of visits to the specialist outpatient clinics (SOCs) and the names of the specialities;Number of visits to the polyclinics and their corresponding primary diagnosis;Total bill sizes, drug costs and bill breakdowns for the visits to emergency departments, hospitalisations, SOCs and polyclinics.

Data extraction from the Electronic Polyclinic Outpatient System (ePOS) and Oracle Business Intelligence (BI) platforms will be performed for the institutions under the purview of NUHS. These institutions include Alexandra Hospital, Ng Teng Fong General Hospital and National University Hospital.

## Outcome measures

### Primary outcome

Change in HbA1c levels in patients receiving the CSP intervention compared with patients receiving standard care from baseline to the study endpoint as defined by the second annual review

The latest HbA1c reading prior to the first annual review will be taken as the baseline and the HbA1c on the second annual review will be taken as the endpoint. The baseline and endpoint for the other variables will be selected on a similar basis.

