## Methods/design

PACE-D is a pragmatic non-randomised controlled trial that evaluates the effects of personalised CSP on persons living with diabetes over two annual reviews with two groups: Intervention experiences personalised CSP; and Control continues with the current care model. Figure 1 illustrates the flow diagram for study participants.

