## Trial intervention

### Current model for Diabetes care

At NUP polyclinics, patients with diabetes undergo an annual panel of laboratory tests in accordance with local clinical guidelines [28]. This includes the HbA1c, fasting capillary glucose, lipid profile, renal function, and urine albumin:creatinine ratio. The patient attends an annual review consultation in the following week with his/her teamlet HCP who jointly reviews the patient and laboratory test results. Depending on the patient’s condition and its control, he/she will be scheduled to attend one or more interim reviews (with laboratory tests performed as indicated) before the following annual review consultation.

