## Statistical methods

### Statistical analyses

Descriptive statistics of the baseline data will be reported, and exploratory data analysis will be conducted prior to model building. Continuous variables will first be tested for normality of distribution. Bivariate analyses will be conducted for continuous variables, and chi-squared test or Fisher’s exact test for categorical variables will be used to determine statistically significant differences between the Intervention and the Control for each baseline characteristic. The analysis will be conducted with the intention-to-treat (ITT) principle unless otherwise specified. Missing endpoints will be imputed with the last observation carried forward (LOCF).

Generalised linear regression will be used to analyse the study endpoint (HbA1c) and while controlling for baseline HbA1c as a covariate. PAM-13 score and other secondary continuous outcomes variables will follow the same analysis methods unless otherwise stated. Logistic regression will be utilised to assess binary outcomes such as screening compliance in the past year, smoking status, and frequent exercise status. Covariates and interaction terms to be included in the model will be selected through inquiry of the data and reviewing existing literature. A stepwise process will be used to drop covariates that have a *p*-value greater than or equal to 0.2. Akaike information criterion (AIC) will be used to decide on the linear model used for potentially non-normal dependent variables such as total cost. Covariates included in the various models will be reported. The outcomes will be compared between the Intervention and the Control. Statistical tests will be conducted at a 2-sided alpha level of 0.05 with confidence intervals calculated at 95%, 2-sided unless otherwise stated. All analysis will be conducted using the STATA software version 16.

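### With clinics designated to arms and only one pre-intervention HbA1c in the primary model, a pre-existing difference in level or trend can be partly or fully read as a CSP effect, and the planned HbA1c analysis cannot detect it

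*Protocol article*

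**What the plan says.** All references are to the Protocol article.

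- Methods/design: "PACE-D is a pragmatic non-randomised controlled trial".
- Study setting: four polyclinics take part, "with two of them designated as Intervention and the other two as Control", and "In each of these polyclinics, one teamlet is involved in the study". The comparison therefore rests on four care teams.
- Primary outcome: the measure is worded as a change, "Change in HbA1c levels in patients receiving the CSP intervention compared with patients receiving standard care from baseline to the study endpoint". It uses one value before CSP ("The latest HbA1c reading prior to the first annual review will be taken as the baseline") and one after ("the HbA1c on the second annual review will be taken as the endpoint").
- Statistical analyses: "Generalised linear regression will be used to analyse the study endpoint (HbA1c) and while controlling for baseline HbA1c as a covariate". Further covariates are to come from data inquiry, literature and a stepwise rule. No earlier HbA1c, pre-intervention trend or clinic term is named for this outcome.
- Current model for Diabetes care: "patients with diabetes undergo an annual panel of laboratory tests in accordance with local clinical guidelines", and the panel includes HbA1c. Clinical data collection and follow-up assessments says that the clinical outcomes are routine data taken from the electronic medical record (EMR).
- Healthcare cost and utilisation, under Statistical methods: the plan looks back one year for cost and utilisation and names difference-in-difference as an option for cost. It offers nothing of the kind for HbA1c.

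**The concern.** In a randomised trial one baseline is enough, because the arms have the same expected level and course before treatment. Designated clinics carry no such guarantee. The arms may have different usual HbA1c, through case mix or the habits of one teamlet, or may already be moving at different rates.

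A single reading is a noisy measure of a patient's usual level, so adjusting for it removes only part of a stable difference. The rest falls into the arm coefficient and favours the arm with the lower usual HbA1c. A difference in pre-existing trend is not removed at all. One reading before CSP also gives no means of seeing whether the arms were running in parallel. What is at stake is how far a difference at the second annual review may be attributed to CSP, which is the primary objective.

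**Working it through.** **Inputs from the document.** N = 1620, 1:1 allocation, six subgroups, difference 0.5 points, 90% power, alpha 0.05, attrition 30% (Sample size calculation); two-sided testing and baseline-adjusted regression (Statistical analyses).

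**Assumptions.** D (stable between-arm difference), g (between-arm difference in trend per year), r (within-arm correlation, equal between any two annual readings) and the SD of HbA1c. The document gives none of them.

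**SD implied by N.** With 2 × (1.96 + 1.2816)² × SD² / 0.5² per arm and subgroup, an SD of about 1.052 to 1.057 gives 94. Then 94 / 0.7 rounds up to 135, and 135 × 12 = 1620. I use SD 1.06, which gives 1632. This only supplies an SD; the sample size is not in question here.

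**Standard error of the planned model.** Completers per arm: 1620 × 0.7 / 2 = 567. SE = SD × √(1 − r²) × √(2/567). At r = 0.7 this is 1.06 × 0.714 × 0.0594 = 0.045. Patients are treated as independent and carried-forward values are not modelled.

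**Bias when CSP has no effect.** Let the arms differ by D at the first annual review and by D + g a year later. The baseline-adjusted estimate is (D + g) − r × D = (1 − r) × D + g. A plain change score gives (D + g) − D = g.

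| Assumed difference | Bias, r from 0.8 down to 0.5 | False-positive rate |
|---|---|---|
| D = 0.2, g = 0 | 0.04 to 0.10 | 19% to 45% |
| D = 0.3, g = 0 | 0.06 to 0.15 | 36% to 79% |
| D = 0.5, g = 0 | 0.10 to 0.25 | 75% to 100% |
| D = 0, g = 0.1/year | about 0.1 | 45% to 75% (highest at r = 0.8) |
| D = 0, g = 0.2/year | about 0.2 | 96% to 100% |

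**Simulation** (1000 runs, r = 0.7, SD 1.06, no CSP effect; bias and false-positive rate):

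| Analysis | D = 0.3, no trend | Trend 0.15/year, arms level at first review |
|---|---|---|
| Planned model, one baseline | 0.09, 51% | 0.15, 92% |
| Change score | 0.00, 4% | 0.15, 87% |
| Three pre-values as covariates | 0.04, 15% | 0.28, 100% |
| Contrast net of pre-trend | 0.00, 5% | 0.00, 4% |

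**Why the earlier value should not be a plain covariate.** With one earlier value added, each pre-value has coefficient r/(1 + r). The level bias falls to (1 − r)/(1 + r) × D: for D = 0.3 and r = 0.7, from 0.09 to 0.053. But if the arms are level at the first review and differ by −g a year before, the estimate becomes g × (1 + r/(1 + r)): for g = 0.15, 0.15 × 1.412 = 0.21 instead of 0.15.

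**What the pre-period can show.** The arms differ by D − g a year before baseline. The same model run one year earlier gives D − r × (D − g) = (1 − r) × D + r × g, which is non-zero under either problem unless the two terms cancel. The difference-in-differences net of the pre-period change gives g − g = 0.

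**Its precision.** That contrast is endpoint − 2 × baseline + prior value, with variance SD² × 6(1 − r), against SD² × (1 − r²) for the planned model. The SE ratio is √(6/(1 + r)) = √(6/1.7) = 1.9 at r = 0.7.

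**The case against.** **A reader might infer that any clinic difference will be read in full as a CSP effect.** The document does not support that. The planned model adjusts for baseline HbA1c and so removes a share r of a stable difference; a plain change score, as the outcome is worded, would remove all of it. Nothing shows that the clinics differ in level or trend. The word is *can*, and for level only *partly*.

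**The sizes rest on assumptions.** This stands. The bias does not depend on the SD, but the false-positive rates do. With an SD of 1.2 to 1.5 and D = 0.3, the expected z is about 1.1 to 1.4 at r = 0.8 and 1.7 to 2.1 at r = 0.6. Other covariates, such as demographics, comorbidities and diabetes medication status, may also shrink D.

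**Earlier values may not be there.** It is tempting to say that they sit in the EMR for every participant. That is a fair inference from the routine annual panel and the EMR extraction, but the document does not state it. Eligibility sets no minimum time since diagnosis or with the teamlet, so some patients will have none.

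**The design is openly non-randomised, and sensitivity analyses belong in the analysis plan.** The openness is to the plan's credit, and the absence of a particular sensitivity analysis would not by itself be a finding. But the article fixes both the single baseline and the adjusted model for designated clinics, and together these allow the bias. It also already uses a one-year look-back for cost and utilisation, so a pre-period for HbA1c is within its own practice.

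**Pre-trend data do not rescue a two-against-two comparison.** Also true. There are only 6 ways to assign four clinics two to an arm, so a clinic-level two-sided permutation p-value cannot fall below 2/6 = 1/3.

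**Conclusion.** The concern holds in a limited form. With one pre-intervention HbA1c used as a covariate in designated clinics, a stable arm difference can leave (1 − r) × D and a differing trend about g in the CSP estimate. The planned HbA1c analysis cannot show whether either is present. For D = 0.3 to 0.5 and r between 0.5 and 0.8, the level bias is 0.06 to 0.25 points, or 12% to 50% of the 0.5-point difference that the plan calls clinically meaningful. A trend difference of 0.1 per year would contribute about 0.1.

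This rests on assumed D, g and r, equal correlation between annual readings, and no other covariates; the false-positive rates also assume an SD of 1.06 and independent patients. It is not evidence that the trial's result will be biased. It is a cheap improvement that should be made because it affects what may be attributed to CSP.

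**What to change.** Keep the planned primary model and add the following before outcome data are examined:

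1. Where available, extract each participant's HbA1c from the routine annual panel about one year, and if possible two years, before the first-annual-review panel.
2. Pre-specify a placebo contrast: the same model one year earlier, with baseline HbA1c regressed on arm and prior-year HbA1c. Show it by arm and by clinic, with its confidence interval, beside the primary result.
3. Always report a difference-in-differences estimate net of the pre-period change as a sensitivity analysis. Do not make it depend on the placebo result: a trigger would make the choice of estimator data-dependent, and level and trend terms can cancel in the placebo contrast.
4. State that the causal claim will be limited if these results disagree with the primary one.
5. Do not enter the prior value as a plain covariate in the primary model, since that can enlarge trend bias.

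Costs: one retrospective EMR extraction and possibly a wording change to the data-access approval. Newly diagnosed or newly empanelled patients will lack a prior value and are left out of these supporting analyses. The trend-adjusted estimate has an SE about 1.9 times that of the primary model at r = 0.7, and it assumes that the pre-period difference in course would have continued. None of this cures having only four clusters.
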